### Allocation and blinding

Participants who provide written informed consent and pass all screening procedures will be randomly assigned at a 1:1 ratio to one of the two trial arms. A researcher ([name]), who is not involved in the implementation of the current trial, will generate the randomisation sequence using a web-based randomisation system [63]. To avoid predictability of group allocation, the system will build permuted blocks of random sizes, namely two, four, six, and eight, with a list length of 20 [33]. The randomisation sequence and the block sizes will not be disclosed to trial implementers. To ensure concealment, [name] will prepare and store sequentially numbered, sealed, opaque envelopes containing information on group allocation for each participant. She will not open the envelope assigned to a participant until he or she has been included in the trial by [name]. [name] will also inform participants by telephone about their group assignment.

Due to the nature of our study design, participants cannot be blinded to treatment allocation. There can also be no blinding of assessors and teachers. However, assessments will be predominantly computer-based and standardised to reduce test leader effects.

### Data collection and management

[name] and trained research assistants will conduct the assessments. To limit the impact of the test leader on results, we aim to ensure that for each participant at least pre- and post-assessments will be conducted by the same assessor. For every assessor, the number of assessments will be balanced between groups.

Data will be saved and stored according to the DSGVO. At the start of the study, every participant will be allotted a unique identification number. Only persons involved in study conduct will have access to the connection code and the data. As assessments will be mainly conducted via computer, most data will be generated and saved automatically. Data from paper documents will be continuously entered into the database throughout the study period and will be kept in a locked cabin. All electronic data will be stored on a secure server and password-protected computers of the NAR. Additional password protection for electronic documents with identifying participant information will be provided. To promote data quality, we will check data randomly throughout study conduct. Missing data will be addressed as quickly as possible. Before the start of the analysis, we will recheck all data for completeness and correctness. We will fully anonymise data upon completion of data collection, at the latest by 31 March 2021.

### Monitoring

Adverse events will be assessed as part of routine monitoring. No formal data monitoring committee will be established, as this study will involve mostly standardised cognitive assessments. Also, foreign language training poses only a minimal risk of adverse events and will be of short duration. The principal author ([name]) is responsible for trial conduct. She will continuously discuss with the immediate trial team all aspects concerning participant safety, study design, and data management. Participants will be informed that they can contact the study team at any time if they have questions or concerns about the study. Any adverse event related or potentially related to study participation will be instantaneously reported to the immediate trial team, the sponsor, and the local ethics committee.

### Statistical analysis

Statistical analysis will be conducted using IBM SPSS Statistics 26 (IBM Corporation: Armonk, NY, USA). We will use the intention-to-treat dataset, considering all participants as randomised who have completed at least pre-assessment and regardless of adherence to protocol. Hypotheses will be tested two-sided on an alpha level of α ≤ .05, which will be adjusted for multiplicity for primary outcomes by applying the Bonferroni correction. Multiple imputation techniques will be applied to account for missing data assuming that data are missing at random (MAR). Additionally, we will report reasons for withdrawal and analyse them qualitatively.

Primary and secondary outcomes will be analysed using 2 (group) × 3 (time) repeated measures analysis of variance (ANOVAs) with group as between-subjects factor and time-point of assessment (pre-, post-, 3-month follow-up) as within-subjects factor. Bonferroni’s post hoc test will be conducted to test hypotheses. We predict a significant group x time interaction, in which the LLG will outperform the WLCG at post- compared to pre-assessment (hypothesis 1) and at 3-month follow-up compared to pre-assessment (hypothesis 2). Partial eta square (*η*_*p*_^2^) will be used as an indicator of effect size.

For the LLG, exploratory subgroup analyses will be performed to evaluate whether effects of foreign language learning on cognitive outcomes are dependent on different levels of cognitive reserve (hypothesis 3) and foreign language knowledge and usage (hypothesis 4). Therefore, we will conduct multiple and simple regression analyses, respectively. The difference in primary outcome measures between pre- and post-assessment will be defined as the dependent variable. Age and indicators of cognitive reserve (CRI-Education, CRI-WorkingActivity, CRI-LeisureTime, and CRI-Index) (hypothesis 3) and the LSBQ-score (hypothesis 4) will be considered as independent variables.

Additionally, we will investigate whether short-term effects of foreign language learning on cognitive measures also apply to the WLCG after completing the control group programme. For this purpose, the WLCG will serve as its control. Using *t*-tests for dependent means, we predict a significant difference between the difference scores from 3- to 4-month follow-up compared to the difference scores from pre- to post-assessment.

To assess the robustness of results, we will perform sensitivity analyses for the following:
We will examine the influence of protocol non-adherence by comparing the intention-to-treat to the per-protocol dataset. Participants will be included in the per-protocol dataset if they have completed at least pre- and post-assessment and a minimum of 14 h of formal language instruction (> 62% of the total course duration) referring to Bak et al. [26].Effects of missing values will be assessed by comparing results from the complete case (only including subjects without any missing values) to the imputed dataset.

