#### Primary outcomes

The Stroop Interference Test (STROOP, test form: S7) [48] and the Divided Attention, a subtest of the Perception and Attention Function Battery (WAFG, test form: S3) [49], are the two primary outcome measures.

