### Sample size

Sample size calculation was based on the main (first) research question for the two primary outcomes, the STROOP and the WAFG, and was conducted using G*Power (version 3.1.9.2). The alpha level was set to α = .05 with the power to detect significant differences of 0.8. A total of *N* = 42 participants will be needed to detect a medium effect size of *d* = 0.25 [24, 26, 62] between pre- and post-assessment, assuming a correlation between repeated measures of *r* = .5. We will adjust for multiple comparisons using the Bonferroni correction. A total sample size of *N* = 60, with *n* = 30 individuals per group, will be required to account for a 30% drop-out rate [24].

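### Holm's step-down procedure would recover power that the plain Bonferroni correction loses on the two primary outcomes, at the same 5% familywise error and the same sample size

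*Protocol article*

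**What the plan says.** In the protocol article, Primary outcomes names STROOP (naming interference tendency) and WAFG, which "are the two primary outcome measures". Statistical analysis sets the error rate: "Hypotheses will be tested two-sided on an alpha level of α ≤ .05". The same sentence then says how that level is handled when there are two endpoints: "which will be adjusted for multiplicity for primary outcomes by applying the Bonferroni correction". Sample size names the same method: "We will adjust for multiple comparisons using the Bonferroni correction". With two outcomes this means .025 for each. No step-down, hierarchical or gatekeeping procedure is mentioned.

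Statistical analysis also plans Bonferroni post hoc tests within each repeated-measures ANOVA. That is a separate layer and is not the subject of this point.

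**The concern.** Plain Bonferroni holds each primary outcome to .025 even when the other has already been shown. Suppose STROOP gives p = .01 and WAFG p = .04. The plan must call WAFG non-significant, whereas Holm would declare both at the same familywise error of 5%. The reverse cannot happen: Holm never misses a rejection that Bonferroni makes.

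The loss is largest when both effects are real, and that is what this trial predicts. Aims explains that both tasks were chosen because language learning should act on the attentional control they share, and Statistical analysis predicts a group-by-time interaction for the outcomes. With 60 participants randomised and 42 assumed evaluable, there is little power to spare for the second outcome.

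**Working it through.** **Inputs from the article**

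- Sample size: "The alpha level was set to α = .05 with the power to detect significant differences of 0.8"; 42 "participants will be needed to detect a medium effect size of *d* = 0.25"; "assuming a correlation between repeated measures of *r* = .5"; 30% drop-out; based on the pre-to-post comparison ("Sample size calculation was based on the main (first) research question for the two primary outcomes").
- Study design and setting: two groups, 1:1.
- Not given: the correlation between the two primary outcomes. It is assumed, with a range of 0 to .7.

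**1. Reproducing N = 42.** For the within-between interaction of a repeated-measures ANOVA, with g = 2 groups, m = 2 measurements and ρ = .5:

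λ = f² × N × m / (1 − ρ), df1 = (g − 1)(m − 1), df2 = (N − g)(m − 1).

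Reading 0.25 as Cohen's f, N = 42 gives λ = 0.0625 × 42 × 2 / 0.5 = 10.5 on 1 and 40 df.

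| Two-sided alpha | Smallest even N for 80% power | Power at N = 42 |
|---|---|---|
| .05 | 34 | .885 |
| .025 | 42 | .815 |

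The stated 42 therefore already contains the Bonferroni split, and 42 / 0.7 = 60. It does not reproduce if 0.25 is a standardised mean difference as labelled (f = 0.125): the same formula then needs 156.

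**2. Holm against Bonferroni, independent outcomes, by hand.** Let a be the power at .025 and b the power at .05 for each outcome.

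- Bonferroni: a per outcome; a² for both.
- Holm: a + a(b − a) per outcome; a² + 2a(b − a) for both.

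With a = .80 the noncentrality is z(.9875) + z(.80) = 2.241 + 0.842 = 3.083, so b = Φ(3.083 − 1.960) = .869. Holm then gives .80 + .80 × .069 = .855 per outcome and .64 + 2 × .80 × .069 = .75 for both, against .64.

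With a = .50, b = Φ(2.241 − 1.960) = .611. Holm gives .50 + .50 × .111 = .555 per outcome and .25 + 2 × .50 × .111 = .36 for both, against .25.

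**3. Correlated outcomes.** Simulation with 1,000,000 draws of bivariate normal test statistics, correlation 0 to .5:

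| Power per outcome at .025 | Per outcome, Holm | Both, Bonferroni | Both, Holm |
|---|---|---|---|
| .80 | about .85 | .64–.69 | .75–.78 |
| .50 | about .55 | .25–.33 | .36–.44 |

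**4. The same with t statistics at the planned N.** N = 42, f = 0.25 on both outcomes, 1,000,000 draws:

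| Correlation | Per outcome, Bonferroni | Per outcome, Holm | Both, Bonferroni | Both, Holm | At least one, either method |
|---|---|---|---|---|---|
| 0 | .815 | .873 | .665 | .780 | .966 |
| .3 | .815 | .866 | .687 | .790 | .943 |
| .5 | .815 | .862 | .706 | .801 | .924 |
| .7 | .815 | .857 | .730 | .815 | .899 |

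If all 60 participants contributed full information, power per outcome would go from .939 to .959–.966 and power for both from .882–.903 to .935–.943.

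**5. Error rate.** With no effect on either outcome, the familywise error is identical for the two methods: .050, .048, .047 and .043 at the four correlations. With an effect on one outcome only, Holm rejects the true null in .041–.045 of trials (Bonferroni .025), still below .05.

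**The case against.** Bonferroni is valid under any dependence, is named consistently in both sections, and its cost is already covered: at .025 each outcome has .815 power, above the 80% target. Nothing in the article makes significance on both outcomes a condition of success, and the chance of showing at least one effect is the same under both methods. If only one effect is real, power for it rises only from .815 to about .817. If drop-out is below 30%, or multiple imputation recovers much of the lost information, the gain on both outcomes shrinks towards the 4 to 5 points seen at N = 60. All of this stands. It limits the size of the benefit, but none of it gives a reason to prefer Bonferroni for the tests.

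Two practical objections carry more weight. First, simple 97.5% intervals can disagree with Holm: an outcome declared significant at p = .03 has a 97.5% interval that includes no effect. The article names partial eta squared as its effect-size indicator and plans no simultaneous intervals, so the loss is modest, but it is real. Second, Trial status reports 54 participants enrolled at submission, and Allocation and blinding says assessors are not blinded. A less strict rejection rule adopted that late must be visibly independent of the results.

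It can also be said that Holm needs to know which p-value it orders, the overall interaction or the pre-to-post contrast. The planned Bonferroni split leaves the same question open, so this is no argument against Holm.

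**Conclusion.** The concern holds. It is an avoidable loss of efficiency, not an error: the planned analysis controls its error rate and meets its own power target. At N = 42, with both effects at f = 0.25, Holm adds about 4 to 6 percentage points of power per outcome and about 8 to 11 points for showing both, over correlations of 0 to .7. With no drop-out, the gain on both is about 4 to 5 points.

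These figures rest on both effects being real, on the assumed correlation range, on one test per primary outcome, and on reading the stated effect size as Cohen's f. The case with 50% power is an illustration of a smaller true effect and does not come from the article. That Holm rejects at least as much as Bonferroni at the same familywise error depends on none of these assumptions. The change is worth making.

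**What to change.** In Sample size and in Statistical analysis, replace the Bonferroni correction across the two primary outcomes by the Holm step-down procedure: the smaller of the two p-values is tested at .025 and, only if it is significant, the larger at .05. State in the same sentence which p-value per outcome is meant; the sample size calculation points to the pre-to-post group-by-time comparison. Leave the Bonferroni post hoc tests within each ANOVA as a separate matter.

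Report 97.5% confidence intervals beside the Holm decisions, with a note that the interval for an outcome rejected at the second step may include no effect.

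Record the change as a dated amendment before any outcome data are examined by group. It needs no extra participants, no new assumption and no new software, since two p-values can be ordered by hand. The 42 evaluable and 60 randomised participants remain as planned.

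### The planned repeated-measures ANOVA uses the pre-assessment as an outcome; adjusting for it instead would cut the variance of the key contrasts by about a quarter at the plan's own r = .5

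*Protocol article*

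**What the plan says.** The Statistical analysis section of the protocol article sets the model: "Primary and secondary outcomes will be analysed using 2 (group) × 3 (time) repeated measures analysis of variance (ANOVAs". The within-subjects factor is "time-point of assessment (pre-, post-, 3-month follow-up) as within-subjects factor", so the pre-assessment enters as an outcome level. Hypothesis 1 is read from the interaction as the prediction that "the LLG will outperform the WLCG at post- compared to pre-assessment (hypothesis 1"; hypothesis 2 is the same comparison at 3 months. Bonferroni post hoc tests carry the hypotheses, and partial eta squared is the named effect size.

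No baseline covariate is named for any primary or secondary outcome. The sensitivity analyses cover adherence and missing data only. For missing values the plan says "Multiple imputation techniques will be applied to account for missing data assuming that data are missing at random (MAR".

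The Sample size section sizes the trial on the pre-to-post comparison, "assuming a correlation between repeated measures of *r* = .5". The Participant timeline section has both groups take the pre-assessment before the course or waiting period starts.

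**The concern.** In a randomised trial the two arms have the same expected baseline, so any observed baseline difference is chance. A change score subtracts the whole pre-assessment score, as if the slope of post on pre were 1. With equal variances and r = .5 that slope is only .5. Subtracting the full score therefore adds noise that a fitted slope would leave out.

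The same over-correction makes the change contrast respond to chance imbalance. With 21 per arm, the standard error of the baseline difference is √(2/21) = 0.31 SD. At r = .5, a chance difference of 0.3 SD shifts the expected change contrast by (1 − .5) × 0.3 = 0.15 SD through regression to the mean. Baseline adjustment takes this out.

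What is at stake is precision in a small trial: 60 randomised, 42 expected to be evaluable, and alpha shared between two primary outcomes. The baseline that would supply the extra precision is already measured in everyone.

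**Working it through.** **Inputs.** From Sample size: r = .5, effect size 0.25, alpha .05, power 0.8, N = 42 evaluable, N = 60 after 30% drop-out, Bonferroni correction. From Statistical analysis: two-sided tests. From Study design and setting: 1:1 allocation. Two primary outcomes give alpha = .05/2 = .025 each. Assumption: equal variance σ² at pre and post.

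**1. Reproduce N = 42.** For a group × time interaction with k = 2 groups and m = 2 times (pre, post), the noncentrality is λ = f²·N·m/(1 − r), on (k−1)(m−1) and (N−k)(m−1) degrees of freedom.
- With f = 0.25: λ = 0.0625 × 42 × 2/0.5 = 10.5 on 1 and 40 df. Power at alpha .025 is 0.815.
- N = 42 is the smallest even N that reaches 0.80, and 42/0.7 = 60.
- The figure reproduces only with 0.25 entered as Cohen's f, although the text labels it d. That labelling does not affect the variance ratio below.

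**2. The same test as a change-score comparison.** For a between-group difference in change D (in SDs of one assessment), λ = D²·(N/4)/[2(1 − r)]. Setting this equal to step 1 gives D = 4f = 1.0 SD. Check: 1.0² × 10.5/1.0 = 10.5. In a simulated 2 × 3 data set, the ANOVA's group × (post − pre) and group × (3-month − pre) estimates equalled the differences in mean change to all printed digits.

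**3. Variances.**
- Change score: 2(1 − r)σ² = 1.00σ² at r = .5.
- Baseline-adjusted: (1 − r²)σ² = 0.75σ² at r = .5.
- Ratio: (1 − r²)/[2(1 − r)] = (1 + r)/2.

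| r | ratio | reduction |
|---|---|---|
| .3 | 0.65 | 35% |
| .5 | 0.75 | 25% |
| .7 | 0.85 | 15% |
| .8 | 0.90 | 10% |
| .9 | 0.95 | 5% |

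**4. Small-sample cost.** Estimating the slope multiplies the adjusted variance by about 1 + 1/(N − 4) = 1 + 1/38 = 1.026 at N = 42. At r = .5 the ratio becomes 0.75 × 1.026 = 0.77. A 20,000-run simulation with 21 per arm gave 0.0735/0.0953 = 0.77, a reduction of about 23%.

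**5. Power at the plan's own effect** (D = 1.0 SD, alpha .025, N = 42).
- Change score: λ = 10.5, 40 df, power 0.815.
- Adjusted: λ = 10.5/0.75 = 14.0, 39 df, power 0.916.
- Adjusted with the small-sample cost: λ = 10.5/0.77 = 13.6, power about 0.91.
- Evaluable N for 80% power falls from 42 to 32, or to 34 once the small-sample cost is charged.

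**The case against.** The strongest reply is that this is a preference between valid estimators. The ANOVA is unbiased under randomisation, its contrasts match the hypotheses as written, and N = 42 reproduces from the same interaction, so design and analysis agree. All of that stands. The point is lost efficiency, which is available at almost no cost.

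The gain is also uncertain. It shrinks as r rises, and r = .5 is a planning assumption. The documents give no test-retest correlation; the reliability coefficients quoted for the two primary tests are not retest values. At N = 42 the adjusted estimate would be very slightly less precise than the change score above about r = .95, so adjustment is not superior in every conceivable case.

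A reader might infer more than the documents support:
- **That the whole 2 × 3 ANOVA is a change-score test.** The omnibus interaction has 2 degrees of freedom and also includes post versus follow-up. The identity holds for the individual contrasts with pre.
- **That multiple imputation cannot be combined with this ANOVA.** The post hoc contrasts are mean differences with standard errors, which Rubin's rules can pool.
- **That the chosen model leaves the trial short of its stated power.** At the effect that N = 42 implies, the planned test already reaches 0.815. Whether a 1.0 SD difference is realistic is a separate sample-size question.

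**Conclusion.** The point holds as a matter of efficiency. The contrasts testing hypotheses 1 and 2 are comparisons of change, and nothing in the protocol article adjusts them for baseline. Using the pre-assessment as a covariate would reduce their variance by 25% at the plan's r = .5, or about 23% at 42 evaluable participants. At the planned effect, power would rise from 0.815 to about 0.91.

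This rests on equal variances at pre and post and on the plan's assumed correlation; at r = .9 the large-sample gain is only 5%. It would be wrong to read the finding as saying that the planned ANOVA is biased or invalid. Randomisation protects it, and the documents give no reason to think otherwise.

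**What to change.** Make the primary analysis a baseline-adjusted comparison of the post and 3-month scores. This can be ANCOVA at each time point, or a linear mixed model with group, time, group × time and pre-score × time. A mixed model with baseline means constrained equal across arms would also serve. Report the adjusted LLG − WLCG difference at post and at 3 months with confidence intervals.

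The planned multiple imputation and the complete-case comparison can stay, with the adjusted differences pooled by Rubin's rules. The 2 × 3 ANOVA and partial eta squared can be kept as secondary.

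The cost is one or two degrees of freedom and no new data. Because the Trial status section reports 54 participants already enrolled and assessors are not blinded, the change needs a dated, documented amendment made before any analysis.

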Our study will have several strengths and limitations. One limitation is that the comparator is only a passive control condition. It is included to monitor improvements in cognitive performance through repeated measurements. The use of a passive control as the only comparison group has already been subject of extensive debate. Some authors argue that clinical trials should ideally include an active control of similar duration and intensity to control for effects attributable to specific treatment modalities, e.g. social activity [21, 64]. However, the inclusion of an active comparator depends on the research question. To date, foreign language learning has not provided clear evidence of maintaining or improving cognitive performance in older adults [21]. Thus, from an economic perspective, it is necessary to examine its effectiveness against a passive control before controlling for other influences or demonstrating its superiority over other activities [65]. Therefore, we decided not to include an active comparator. To still be able to differentiate effects of the intervention from more general effects, we included some secondary outcomes which should not benefit from foreign language learning. This can be presumed because verbal fluency and non-executive components of attention largely relate to cognitive functions which might be less affected by foreign language learning. Furthermore, a significant regression of previous foreign language skills and usage on our results could also be informative. Different levels of cognitive reserve have already been associated with changes in cognition after cognitive training [31]. Thus, assuming previous foreign language skills and usage are part of cognitive reserve, varying results depending on prior skills could indicate a direct effect of language training.

To our knowledge, we are conducting the first randomised controlled trial of its kind with a short and intensive foreign language training. We opted for this approach, as more intensive and short foreign language learning programmes were more likely to be associated with cognitive improvements than less intense trainings with longer durations [24–26, 28]. Furthermore, this short intervention period increases our chances of achieving the targeted sample size, since older adults, although retired, often lead an active lifestyle, and thus have limited time resources.

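### Regressing change in the language group alone can show who changes, but not whether the course effect depends on cognitive reserve or prior language use (hypotheses 3 and 4)

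*Protocol article*

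**What the plan says.** The Statistical analysis section sets the question and the population together: "For the LLG, exploratory subgroup analyses will be performed to evaluate whether effects of foreign language learning on cognitive outcomes are dependent on" levels of cognitive reserve (hypothesis 3) and of foreign language knowledge and usage (hypothesis 4). It then fixes the model. "The difference in primary outcome measures between pre- and post-assessment will be defined as the dependent variable". The predictors are age and the CRI scores for hypothesis 3 (multiple regression) and the LSBQ score for hypothesis 4 (simple regression). The model contains no waiting-list data, no group term, no group by moderator term and no baseline score. The analyses are labelled exploratory.

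Three other places bear on this:

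- Aims words hypotheses 3 and 4 more softly: reserve and prior language use are expected to predict changes in cognitive scores.
- The Discussion says the passive control is there to capture improvement that comes from repeated testing. It later says that "varying results depending on prior skills could indicate a direct effect of language training".
- Under Baseline variables and Participant timeline, the CRIq and LSBQ are baseline measures, and further baseline data are collected at the face-to-face screening, before randomisation. They therefore exist for both arms.

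**The concern.** Asking whether the effect of the course depends on a baseline variable is a question about effect modification. It needs a contrast with people who did not take the course. Within the learning group, pre-post change is the sum of the course effect, the gain from sitting the test again, and regression to the mean. If reserve or prior language use is related to either of the last two, the slope will differ from zero even when the course works equally well for everyone, and the same slope would appear in the waiting-list group.

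The protocol brings in the control arm to deal with retest gain for hypotheses 1 and 2, but leaves it out for 3 and 4. What is at stake is the interpretation of the two exploratory hypotheses and the Discussion's suggestion that a slope on prior skills could mark a direct training effect.

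**Working it through.** **The plan's own figure.** No sample size is given for hypotheses 3 and 4. The primary calculation is reproduced here because it supplies the group sizes. It is a noncentral F for the group by time interaction with two time points, effect f = 0.25, repeated-measures correlation 0.5 and alpha .05/2 = .025 ("Hypotheses will be tested two-sided on an alpha level of α ≤ .05, which will be adjusted for multiplicity for primary outcomes"):

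- λ = f² × N × m / (1 − r) = 0.0625 × 42 × 2 / 0.5 = 10.5, on 1 and 40 df, power 0.815.
- 42 / (1 − 0.30) = 60, so 30 per arm; with 30% drop-out, 30 × 0.70 = 21 completers per arm.

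The stated 42 and 60 reproduce with 0.25 entered as f. The relevant sizes for the learning-group regression are therefore n = 30 and n = 21.

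**Chance of a false moderation finding, learning group only.** Assume the course effect is the same for everyone and the moderator has correlation ρ with retest change, equal in both arms. The documents give no ρ, so a range from zero is shown. For a single predictor (the hypothesis 4 model), two-sided alpha .05:

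- Noncentrality = ρ / √(1 − ρ²) × √n, t on n − 2 df.
- Example, ρ = 0.3, n = 30: 0.3 / √0.91 × √30 = 1.72 against a critical value of 2.05, giving 38%.

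| Assumed ρ | n = 30 | n = 21 |
|---|---|---|
| 0 | 5% | 5% |
| 0.1 | 8% | 7% |
| 0.2 | 19% | 14% |
| 0.3 | 38% | 28% |
| 0.4 | 64% | 48% |

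A simulation of 6,000 trials per setting agrees closely: for ρ = 0.2, 0.3 and 0.4 it gives 18%, 38% and 61% (n = 30), and 14%, 27% and 45% (n = 21).

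**Regression to the mean alone.** Take the protocol's pre-post correlation of 0.5 and an assumed moderator-baseline correlation of 0.3 or 0.5. With unit variances, change has variance 2 × (1 − 0.5) = 1, so the moderator's correlation with change has size 0.5 × 0.3 = 0.15 or 0.5 × 0.5 = 0.25. The simulated false-finding rate is 12% or 27% at n = 30, and 10% or 20% at n = 21.

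**Both arms.** In the same simulations, change was also regressed on group, moderator and group × moderator. The interaction was significant in 4.5% to 5.1% of trials in every setting.

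**Precision.** Approximate slope (residual SD per moderator SD) needed for 80% power at two-sided .05, using 1.96 + 0.84 = 2.80:

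- Single-arm slope: 2.80 / √n = 0.51 (n = 30) or 0.61 (n = 21).
- Difference in slopes: 2.80 × √(2/n) = 0.72 (30 per arm) or 0.86 (21 per arm).

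**The case against.** Several points on the other side stand, and they limit the criticism.

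- A reader might infer that hypotheses 3 and 4 are themselves effect-modification hypotheses that the plan fails to test. Aims does not say so. It speaks of predicting change, which one arm can answer. The fault lies between that wording and the Statistical analysis and Discussion sections.
- A reader might infer that any slope will be reported as moderation. The analyses are called exploratory and the Discussion says only that results could indicate a direct effect. The exploratory label, however, concerns strength of evidence. It does not make the model answer the question set for it.
- A reader might infer that the case for a specific language effect rests on this regression. The Discussion relies first on secondary outcomes not expected to benefit; the prior-language regression is an additional argument, and the CRIq regression is not used this way.
- A reader might take 38% to 64% as the expected error rate. Nothing in the documents supports a correlation of 0.3 to 0.4, nor any link between reserve and baseline score. At ρ = 0 the rate is the nominal 5%. The table describes a one-predictor model, so it does not carry over directly to the multiple regression for hypothesis 3.
- Bonferroni is announced for primary outcomes, and the protocol does not say whether it covers these regressions. At .025 the figures for ρ = 0.3 and 0.4 fall to 28% and 52% (n = 30), or 19% and 35% (n = 21).
- The trial was not sized for an interaction, which may well be inconclusive. That is a real cost, but a precise slope that answers a different question does not remove it.

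**Conclusion.** The point holds in a limited form. The Statistical analysis section asks whether the course effect depends on reserve or prior language use and then fixes a model that cannot separate this from prediction of retest gain or from regression to the mean. The logic does not depend on any assumed figure; the size does. The excess over 5% is nil if the moderator is unrelated to retest change and baseline score, and grows as that unknown association grows, as tabulated. Hypotheses 1 and 2 use the group by time interaction in both arms and are unaffected. The change is worth making because the plan allows a mechanistic reading of the prior-language slope and the data for a proper contrast will already be in hand.

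**What to change.** For hypotheses 3 and 4, fit both arms: post score on pre score, group, moderator (CRI-Index or LSBQ score; keep age for hypothesis 3) and group × moderator. Report the interaction with its confidence interval, labelled exploratory. The learning-group slopes may be kept if they are described as predictors of change, in line with Aims. Draw the Discussion's inference about a direct training effect only if the interaction supports it.

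The cost is wording and lower precision: the slope difference detectable with 80% power is √2 times the single-arm slope (0.72 against 0.51 at 30 per arm). No new assessments are needed.
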